## Abstract

Background/Objectives: Histamine intolerance is primarily caused by a deficiency in the diamine oxidase (DAO) enzyme at the intestinal level. The reduced histamine degradation in the gut leads to its accumulation in plasma, thereby causing multiple clinical manifestations, such as urticaria, diarrhea, headache, dyspnea, or tachycardia, among others. The dietary management of this food intolerance consists of the follow-up of a low-histamine diet, often combined with DAO supplementation. To date, around twenty studies have investigated the effectiveness of these dietary strategies in reducing the frequency and/or intensity of symptoms, with promising results. However, the limitations of these studies (small patient cohort, lack of control group, and short dietary intervention periods) highlight the need for more ambitiously designed research. Therefore, the main objective of this prospective, unicentric, double-blind, randomized, and placebo-controlled trial is to evaluate the efficacy of a low-histamine diet and/or DAO supplementation over a three-month period in improving symptoms of histamine intolerance. Additionally, the impacts of these dietary strategies on the intestinal microbiota composition, urinary profile of histamine metabolites, serum DAO activity, and plasma histamine levels will be assessed throughout the intervention. Methods: The trial will enroll 400 patients who will be randomly assigned to one of two groups: the intervention group, which will follow a low-histamine diet, or the control group, which will maintain their habitual dietary habits. Within each of these groups, participants will be further divided into four subgroups to receive either exogenous DAO enzyme supplementation (from porcine or plant sources, with the latter administered at two different dosages) or a placebo. Therefore, a total of eight distinct intervention groups will be considered. The comparison of these groups will allow the evaluation of the individual effects of the low-histamine diet or DAO enzyme supplementation, as well as their possible synergistic effect. Results: The results of this study should help to improve dietary recommendations for histamine-intolerant patients and ultimately enhance their quality of life.

## 1. Introduction

Histamine intolerance is a non-allergic hypersensitivity reaction that occurs in susceptible individuals when they ingest normally tolerable amounts of histamine. This condition arises primarily from deficient intestinal activity of the enzyme diamine oxidase (DAO) [1,2,3], which, by breaking it down, serves as the main barrier to dietary histamine entering systemic circulation. When DAO is deficient, histamine accumulates in the plasma, leading to clinical manifestations of histamine intolerance [4,5,6]. Histamine interacts with four types of histamine receptors in the body, with variable physiological effects. Consequently, symptoms resulting from histamine accumulation can impact multiple organs and tissues (Figure 1). Due to this wide range of effects, patients with histamine intolerance frequently exhibit complex combinations of symptoms [6,7,8,9].

The dietary management of histamine intolerance, aiming to reduce or avoid symptoms, is currently based on the exclusion of histamine-containing foods (i.e., a low-histamine diet), often combined with exogenous DAO supplementation to promote the metabolism of dietary histamine at the intestinal level [10]. There are two types of DAO supplements available on the market. The most common contains an active ingredient of porcine origin, whereas the recently introduced plant-based DAO supplements feature an active ingredient derived from lyophilized legume sprouts.

To date, around twenty studies have investigated the effectiveness of a low-histamine diet [11,12,13,14,15,16,17,18,19,20,21,22,23,24,25,26] or DAO supplementation [27,28,29,30,31] in reducing the frequency and/or intensity of histamine intolerance symptoms, with promising results. However, the limited number of clinical studies, many of them based on small patient groups or short dietary interventions, highlights the need for more ambitiously designed research to draw more accurate conclusions about the clinical effectiveness of these dietary strategies, applied separately or in combination.

Therefore, the main objective of this clinical study is to evaluate the efficacy of a low-histamine diet and/or DAO supplementation over a three-month period in improving symptoms of histamine intolerance caused by DAO deficiency. Additionally, the impacts of these dietary strategies on the composition of intestinal microbiota, urinary profile of histamine metabolites, serum DAO activity, and plasma histamine levels will be assessed throughout the intervention.

## 2. Materials and Methods

### 2.1. Study Design

This prospective, unicentric, double-blind, randomized, and placebo-controlled trial is being performed by a multidisciplinary team of researchers from the Food Bioactive Amines and Polyamines research group at the Food and Nutrition Campus, University of Barcelona, and the Cardiovascular Risk, Nutrition, and Aging research group at the August Pi i Sunyer Biomedical Research Institute (IDIBAPS) of the Hospital Clínic de Barcelona. The study commenced in June 2022 and is expected to conclude in May 2025.

The study design is outlined in Figure 2. In this protocol, participants are randomized into eight study groups (50 individuals/group), based on combinations of diet (low-histamine or control diet) and supplementation (placebo, porcine DAO, and two different doses of plant-based DAO). The intervention period lasts three months.

The sample size is calculated considering the average number of symptoms reported by histamine-intolerant patients and the standard deviation (11.1 symptoms/patient ± 4.8) [6]. To detect a variation in at least two symptoms per patient, assuming an alpha risk of 0.05 and a beta risk of 0.02 in a bilateral contrast, a minimum of 42 participants per group is required. To accommodate a 10% drop-out rate, 50 participants will be recruited for each group. Therefore, as the study includes eight intervention groups, the total number of participants is 400.

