#### 2.1.2. Baseline Visit and Randomization of Participants

During the baseline visit, a trained nurse administers a questionnaire to record demographic data and a complete medical history, including alcohol consumption and smoking habits (Supplementary Figure S1). Additionally, participants complete various validated questionnaires specific to each symptom of histamine intolerance (described below). Comprehensive information on dietary habits is collected through a validated 151-item semi-quantitative food frequency questionnaire (FFQ), a seven-day dietary recall (for the seven days prior to the visit), and either a 14-item Mediterranean diet adherence screener (for control diet) or a low-histamine diet screener, administered by trained dieticians in face-to-face interviews [32].

The same trained personnel then collect anthropometric measurements, determine blood pressure (BP), and extract a blood sample to analyze biochemical parameters. Height is measured to the nearest 0.1 cm using a wall-mounted stadiometer, with subjects standing, wearing socks, and maintaining their heads in the horizontal plane. Body weight is recorded to the nearest 0.1 kg, with participants in light clothing, without shoes or accessories, and using a high-quality calibrated scale. Body mass index is calculated by dividing weight (kg) by the square of height (m^2^). Waist circumference is measured midway between the lowest rib and the iliac crest using an anthropometric tape, and hip circumference is measured at the maximum point below the waist, without compressing the skin [33]. BP is taken in triplicate after at least five minutes of rest using a validated semiautomatic oscillometer (Omron HEM-705CP, Hoofddorp, The Netherlands). The clinical analyses include a basic biochemical profile (i.e., glycemia, lipid profile, creatinine, urea, hepatic function parameters, and total proteins and albumin) and serum histamine and tryptase levels. All these analyses are performed in the CORE laboratory of Hospital Clinic following in-house routine procedures and meet all required quality criteria, receiving ISO 9001:2015 certification [34] and ISO 15189:2022 accreditation [35] for some tests.

At this point, participants provide urine and stool baseline samples for the study of metabolomic biomarkers of histamine and intestinal microbiota, respectively (described below). Samples are processed after collection and stored in −80 °C freezers.

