#### 2.1.3. Dietary Intervention

The low-histamine diet primarily involves the exclusion of foods likely to contain histamine (i.e., fish and its derivatives, fermented products, and certain plant-based foods), as well as foods with high amounts of other biogenic amines, such as citrus fruits, banana, nuts, pumpkin, and zucchini. Although these foods do not contain histamine, they may have significant amounts of putrescine and/or cadaverine, which could trigger the onset of histamine intolerance symptoms due to competition with histamine for degradation by the DAO enzyme [36]. Supplementary Figure S2 contains the dietary recommendations for participants, including a list of foods to consume and to avoid for correct adherence to the low-histamine diet. Participants in the control diet groups continue following their usual dietary habits.

Regarding supplementation, both possible origins of the DAO active ingredient (porcine and vegetal) will be assessed. In order to consider the potential influence of the dose of active ingredient, vegetal DAO supplements at two different doses will be tested. The posology for DAO (regardless of origin and dose) and the placebo involves taking one tablet 20 min before each main meal (three times/day). Porcine DAO supplementation consists of a kidney protein extract (4.2 mg), authorized as a novel food by the European Commission since 2017 [37]. Vegetal DAO supplements are formulated with lyophilized green pea (*Pisum sativum*) sprouts, containing either 4.2 mg or 8.4 mg of the active ingredient per tablet. The placebo tablets consist of microcrystalline cellulose, designed to match the form, size, and color of the DAO supplements. All tablets have an enteric coating to ensure their integrity during passage through the gastric environment. DR Healthcare España S.L.U. (Barcelona, Spain) provides both DAO supplements and placebo tablets.

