#### 2.1.4. Follow-Up and Final Visits

The evolution of symptoms, urinary profile of histamine metabolites, and intestinal microbiota composition, as well as anthropometric measurements and blood biochemical parameters, including the basic biochemical profile and histamine and tryptase, are assessed after the first and second month (follow-up visits) and the third month (final visit) of the dietary intervention (Figure 2). Serum DAO activity will also be measured during the final visit.

Dietary compliance is assessed using seven-day food records and adherence tests for the low-histamine diet or Mediterranean diet [32]. Unlike the validated Mediterranean diet adherence screener, there is no standard test for assessing compliance with a low-histamine diet. The present research will validate the low-histamine diet adherence test prepared *ad hoc* for this study.

Throughout the intervention period, participants receive a phone call every two weeks to assess correct adherence to the study protocol and to monitor for any unexpected secondary effects.

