This study is also designed to provide valuable insights into the prevalence of genetic polymorphisms and levels of DAO activity and plasma histamine in patients with histamine intolerance. These parameters are correlated with the presence, intensity, and evolution of symptoms throughout the dietary intervention. In general, the results of this study should help to improve dietary recommendations for histamine-intolerant patients and ultimately enhance their quality of life.

The primary limitation of this study is that, despite the expected high number of participants (n = 400), the randomization into multiple intervention groups (low-histamine diet versus control, animal- and plant-based supplementation, and two dosage levels of the latter) results in a smaller sample size per group, which could potentially reduce the statistical power of the analyses. To address this, secondary analyses combining specific intervention groups, when methodologically appropriate, can be performed to effectively increase the sample size in those comparisons. Another limitation could be that the unicentric design means findings may not be generalizable to other histamine-intolerant populations and could be subject to selection bias among patients with this food intolerance. Finally, the reliability of dietary records may be influenced by recall bias or social desirability bias.

The main strength of the study is its design as a randomized clinical trial, which allows causal inference. Standardized data collection conditions for anthropometric and blood measurements, as well as for symptom recording and dietary intake frequency using validated questionnaires, are additional strengths. Overall, the findings of this clinical trial will contribute to the development of more effective and tailored dietary interventions for histamine intolerance. Specifically, robust and reliable evidence will be generated regarding the efficacy of the low-histamine diet, the current gold-standard treatment. Furthermore, the study will clarify the role of supplementation in symptom management, including the optimal type and dosage, thereby providing evidence-based recommendations for its use in clinical practice.

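### The double-blind, placebo-controlled label covers the whole trial, but only the tablets are masked: the diet comparison is open-label and is read mainly on self-reported symptoms

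*Protocol article*

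**What the plan says.** Section 2.1 of the protocol article applies the blinding label to the whole study: "This prospective, unicentric, double-blind, randomized, and placebo-controlled trial is being performed". The Abstract uses the same label, and the Discussion attaches it to the combination of diet and DAO supplementation. Two factors are randomized, "based on combinations of diet (low-histamine or control diet) and supplementation (placebo, porcine DAO, and two different doses of plant-based DAO".

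Section 2.1.3 describes masking for the supplement only: "The placebo tablets consist of microcrystalline cellulose, designed to match the form, size, and color of the DAO supplements". For diet, the low-histamine arm gets written recommendations, "including a list of foods to consume and to avoid for correct adherence to the low-histamine diet", while "Participants in the control diet groups continue following their usual dietary habits". Under section 2.1.2 the participant personally draws a separate envelope for diet.

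At the baseline visit (section 2.1.2) dieticians administer, face to face, "either a 14-item Mediterranean diet adherence screener (for control diet) or a low-histamine diet screener". The same section describes randomization only after all the baseline measurements and samples. At follow-up (section 2.1.4), "Dietary compliance is assessed using seven-day food records and adherence tests for the low-histamine diet or Mediterranean diet".

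Section 2.2.1 judges effectiveness from symptom and quality-of-life questionnaires, using covariance analysis with baseline parameters as covariates. The Discussion states that "robust and reliable evidence will be generated regarding the efficacy of the low-histamine diet, the current gold-standard treatment".

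**The concern.** A diet defined by a list of foods to avoid, compared with unchanged eating, cannot be masked from the person eating it. Nothing in the article describes a sham or masked comparison diet. No detail left to a fuller protocol could make these two conditions double-blind.

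This matters because the efficacy of the diet, alone or with DAO, is part of the main objective, and the outcome is mainly what participants report about themselves. A person who knows that he or she is on the diet described as the gold standard may report fewer symptoms for that reason alone. The estimated diet effect then combines food exclusion with expectation, and a reader who trusts the label would credit all of it to food exclusion.

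Two smaller matters follow from the open diet. A baseline form chosen by diet arm presupposes that the arm is known, which does not fit the described visit order. And if each arm is scored on its own adherence test, there is no common score to show how far the arms differed in following the low-histamine diet.

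**Working it through.** The main point needs no arithmetic. It follows from setting the sections side by side.

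**1. What is masked, by factor**
- Supplement: placebo tablets match the active ones (2.1.3). The double-blind label is plausible here.
- Diet: the participant draws the diet envelope (2.1.2) and then gets a food list or keeps the usual diet (2.1.3). The participant knows the arm. A dietician who gives an arm-specific screener face to face knows it too.

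**2. Which comparisons are affected**
- Eight groups give 8 × 7 / 2 = 28 pairwise comparisons.
- Within one diet: 2 × (4 × 3 / 2) = 12. These compare tablets among people on the same known diet and stay masked.
- Across diets: 28 − 12 = 16. These are open, including diet plus DAO against control diet plus placebo.
- The diet main effect is open.
- The interaction (synergy) is estimated across open arms. An expectation effect that simply adds to the diet effect would cancel from it. One that changes how much further improvement a supplement can show would not.

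**3. What the limitations cover**
- The Discussion lists reduced power per group, the single centre with possible selection bias, and recall or social desirability bias in the dietary records. The unmasked diet is not among them.

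**4. Baseline order**
- Section 2.1.2 lists the symptom questionnaires, then the dietary instruments with a screener tied to diet arm, then measurements and samples, and last the randomization.
- Choosing the screener by arm requires the arm to be known. So either allocation is known during part of the baseline visit, or the order is misdescribed. The text does not settle which.

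**5. Adherence measures**
- As sections 2.1.2 and 2.1.4 read, each diet has its own test, and controls are assessed on a Mediterranean diet that nobody assigns to them.
- The food frequency questionnaire and seven-day recall at baseline, and the seven-day records at follow-up, are not split by arm. Intake can be compared between arms; an adherence score cannot.

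**6. Illustration of size (assumed bias; the documents give none)**
- SD 4.8 symptoms and target difference 2 symptoms (2.1). Per diet arm: 4 × 50 = 200, less 10% drop-out = 180.
- SE of the diet difference = 4.8 × √(2/180) = 0.506.
- Assume no true diet effect and an expectation effect of 0.5 or 1 symptom, which is 0.5/2 = 25% or 1/2 = 50% of the target.
- Bias 0.5: shift 0.5/0.506 = 0.99, so P(|z| > 1.96) is about 0.17.
- Bias 1.0: shift 1.0/0.506 = 1.98, so P(|z| > 1.96) is about 0.51.

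**The case against.** An open whole-diet intervention is largely unavoidable, and a reader can see that the placebo refers to tablets. The supplement comparisons are plausibly double-blind, so the label is too broad rather than false. Urinary metabolites, microbiota, serum DAO activity and plasma histamine are laboratory measures that are not self-reported. All of this stands. It does not excuse an unqualified label, or a promise of robust diet evidence that leaves out the limitation.

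A reader might infer several stronger points, which the documents do not support:
- *That the baseline symptom scores used as covariates were taken with allocation known.* Section 2.1.2 lists the symptom questionnaires before the screener, and randomization last. Even if the screener follows the draw, the symptom forms need not. This is an ambiguity to resolve, not a demonstrated bias.
- *That the low-histamine test certainly goes only to the diet arm at follow-up.* Section 2.1.4 does not assign the tests by arm. This is a likely carry-over from section 2.1.2, not a statement.
- *That validation of the new adherence test has no off-diet data.* Section 2.1.1 requires that participants have not started the diet, so any low-histamine screener completed at baseline gives off-diet scores, which can be compared with later scores in the same person. The seven-day records offer a reference.
- *That 17% to 51% estimates this trial's error rate.* It only restates an assumed bias, and on symptom count, whereas section 2.2.1 analyses questionnaire scores.

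**Conclusion.** The point holds for the diet factor. The stated double-blind, placebo-controlled property is absent for the diet main effect and for the 16 of 28 pairwise comparisons that cross diets. The article neither says so nor limits its diet claim. The 12 supplement comparisons within a diet are unaffected.

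The size of any expectation effect cannot be derived from the documents. The illustrative false-positive rates rest on an assumed bias of 0.5 to 1 symptom, no true diet effect, an SD of 4.8 and 180 completers per diet arm. They show only that a bias well below the 2-symptom target would matter on this margin. The conclusion does not depend on them.

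The screener timing is an inconsistency to be clarified. The lack of a common adherence score is how the text reads, and the shared intake instruments partly offset it. This should be corrected, but it does not invalidate the trial.

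**What to change.** - Restrict the double-blind, placebo-controlled label to the supplement comparisons within diet, and state in the Abstract, section 2.1 and the Discussion that the diet comparison is open-label.
- List the open diet as a limitation, limit the diet conclusion to match, and report the laboratory outcomes beside the symptom results as support that does not rest on self-report.
- State in section 2.1.2 that all baseline questionnaires and screeners are completed before any envelope is opened. If that was not the practice, describe the order actually used.
- For remaining participants, give the low-histamine screener to both arms at each visit, asking about intake only. Report the between-arm difference in score, and validate the screener against the seven-day records across both arms.

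The cost is wording, a clear visit order and one short extra form for controls. The diet claim becomes weaker, and the form might hint to controls which foods to avoid, hence intake questions only. The study began in June 2022 and was expected to end in May 2025, so procedural changes cannot reach participants already seen. The relabelling and the limitation apply to the whole trial.

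### The 42 per group in the sample-size paragraph does not give the stated beta of 0.02 for a 2-symptom difference

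*Protocol article*

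**What the plan says.** Section 2.1 (Study Design) takes a mean of 11.1 symptoms per patient with SD 4.8 from a cited source. The target is given as "To detect a variation in at least two symptoms per patient". It then states that, at "an alpha risk of 0.05 and a beta risk of 0.02 in a bilateral contrast, a minimum of 42 participants per group is required". The next step is "To accommodate a 10% drop-out rate, 50 participants will be recruited for each group", which gives 400 over eight groups. The test is described only as a bilateral contrast. No correlation, SD of change or adjusted formula is given.

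Section 2.2.1 plans to compare the study groups by covariance analysis with baseline values as covariates. Section 3 (Discussion) names as the primary limitation that splitting into many groups "results in a smaller sample size per group, which could potentially reduce the statistical power of the analyses". It offers analyses that combine groups as secondary.

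**The concern.** A beta of 0.02 means 98% power, and the paragraph prints every input needed to check the number. A difference of 2 against an SD of 4.8 is a standardised effect of about 0.42, and 42 per group is far too few to detect that with 98% power between two groups. This is a conflict between printed inputs and a printed result, not a detail that a fuller document could supply.

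The article promises to separate the effects of diet and supplement, to look for synergy, and to identify the best type and dose of supplement. Comparisons of single groups, such as one supplement against placebo within one diet, rest on about 45 against 45. A reader who takes the paragraph at its word would treat a null result there as near-conclusive evidence against a 2-symptom effect.

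**Working it through.** **Inputs** (all from section 2.1): SD 4.8; difference 2; two-sided alpha 0.05; beta 0.02; 42 per group; 50 recruited; 10% drop-out; eight equal groups. Normal quantiles: 1.960 (alpha), 2.054 (beta 0.02), 0.842 (beta 0.20).

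**1. Attempt to reproduce 42.**

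Two groups: n = 2(z_alpha + z_beta)²(SD/difference)².
- Beta 0.02: 2 × (1.960 + 2.054)² × 2.4² = 2 × 16.11 × 5.76 = 185.6, so 186 (t-based: 187).
- Beta 0.20: 2 × (1.960 + 0.842)² × 5.76 = 2 × 7.849 × 5.76 = 90.4, so 91 (t-based: 92).

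One sample, taking 4.8 as the SD of change: half of the above.
- Beta 0.02: 92.8, so 93 (t-based: 95).
- Beta 0.20: 45.2, so 46 (t-based: 48).

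Eight-group omnibus test in its most favourable pattern (assumed: four group means 2 symptoms above the other four). The noncentrality is n × 8 × 1²/4.8² = 0.347n on 7 degrees of freedom.
- Beta 0.20: 41.3 by the chi-square approximation (rounds up to 42), or 42.2 by noncentral F. F-test power at 42 is 79.8%.
- Beta 0.02: about 76, so 77.
- If only one group differs by 2, power at 42 is 39%.

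No reading tried gives 42 at beta 0.02 from the stated inputs. Only the favourable omnibus pattern at beta 0.20 reaches it.

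**2. Unadjusted power between two groups for 2 symptoms.** At n = 42 the noncentrality is (2/4.8) × √21 = 1.909. Power is about Φ(1.909 − 1.960) = 48.0%.

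| n per group | Power (noncentral t) |
|---|---|
| 42 | 47% |
| 45 (50 less 10%) | 50% |
| 50 | 54% |

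At 45 per group the detectable difference is about 2.9 symptoms for 80% power and about 4.1 for 98%.

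**3. Covariance analysis.** The residual SD is 4.8 × √(1 − ρ²), where ρ is the correlation of baseline with the final value. The article does not give ρ, so these are assumptions.

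| ρ | Residual SD | Power at 45 per group |
|---|---|---|
| 0.5 | 4.16 | 62% |
| 0.7 | 3.43 | 78% |

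Correlation needed at 42 per group:
- 80% power: √(1 − 42/90.4) = 0.73.
- 98% power: √(1 − 42/185.6) = 0.88.

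**4. Factorial margins with 45 completers per group** (unadjusted, 2 symptoms):
- Diet: 4 × 45 = 180 against 180, 98%.
- One supplement against placebo: 2 × 45 = 90 against 90, 79%.

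Both refer to a 2-symptom effect averaged over the other factor.

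**5. Drop-out step.** 42/0.90 = 46.7, so 47 would be enough. Recruiting 50 leaves 50 × 0.90 = 45, which exceeds 42.

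**The case against.** The strongest reply is that section 2.1 names no test, so a two-group t-test is the reviewer's choice. If beta 0.02 is a misprint for 0.20, 42 can be recovered from the omnibus test above. It can also be recovered from a before-after calculation: with equal SDs at both times n = 90.4 × (1 − ρ), which is 42 at an assumed correlation of about 0.54. This part stands: a reader might infer that 42 is about half of what is needed even at beta 0.20 whatever the test, and the article does not support that. The factor of two holds for a pairwise comparison only. But neither recovery is stated in the article, neither works at the printed beta, and neither powers a comparison of one group with another.

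A second reply is that the planned analysis is adjusted for baseline, so 47 to 50% is not its power. This also stands. The figure is the unadjusted one, and a reader should not infer that every pairwise analysis in the trial is a coin flip. The gain depends on a correlation that the article does not give, and 98% at 42 per group would need about 0.88.

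A third reply is that the Discussion already admits low power. It does so without a figure, and it leaves the beta of 0.02 uncorrected.

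Finally, a reader might infer that the drop-out allowance is wrong because 42 inflated for 10% loss is 47. It is not an error: going to 50 is conservative rounding.

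**Conclusion.** The sample-size statement is wrong as written. At its own inputs a pairwise comparison needs 186 per group, more than four times the 42 stated (186/42 = 4.4). If beta was meant to be 0.20 it needs 91, about twice (91/42 = 2.2). Unadjusted pairwise power for 2 symptoms is 47% at 42 per group and 50% at 45 completers. These figures rest on SD 4.8, a two-sided 5% test of two groups and no adjustment for multiple comparisons.

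They do not show that 400 participants is too few for the trial as a whole. The diet margin has about 98% power and the single-supplement margin about 79%, provided there is no material diet-by-supplement interaction. The Discussion treats such pooled analyses as secondary, however, so they are not the basis that section 2.1 gives for its number. All of this concerns the symptom count used for sizing. It is not the power of the individual questionnaire analyses in section 2.2.1.

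**What to change.** Keep 400 participants and rewrite the sample-size paragraph of section 2.1:

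- Correct beta, and name the test and the comparison that the calculation refers to.
- State that 45 completers per group give about 50% unadjusted power for a 2-symptom difference between two groups, and 80% power for about 2.9 symptoms.
- If a gain from covariance adjustment is claimed, state the baseline correlation relied on and its source.
- Add the power of the factorial margins: diet, 180 against 180, about 98%; one supplement against placebo, 90 against 90, about 79%. Label both as applying to a 2-symptom effect averaged over the other factor, that is, without a material diet-by-supplement interaction.
- Leave the drop-out allowance at 50 per group. Adding that this leaves 45 would make it clear.

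The cost is one reworded paragraph and a less favourable stated power for single-group comparisons. No extra participants and no change in conduct are needed.
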